### Sample Size

The primary outcome will be analyzed using the mixed model repeated measurement (MMRM) method to compare the amount of change between groups before and after the intervention (α .05, β .10). To the best of our knowledge, no previous studies have indicated the effect size of MBPs on presenteeism among employees. The sample size was calculated based on the results of a study that showed the effect of MBPs on the quality of life (effect size=0.44) [37]. We estimated that a total of 166 participants are required; however, the sample size was set at a maximum of 220 participants, considering the dropout rate (assumed to be 25%). The dropout rate was referred to the study of an online MBP in the workplace by Aikens et al [44], which reported the dropout rate was 23%.

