### Randomization

Eligible participants were randomly allocated to either the bMBCT or the waitlist control group (in a 1:1 ratio). The participants were assigned a computer-generated random number stratified according to company and the baseline WHO-HPQ absolute presenteeism score. The Project Management Office at the Keio Center of Clinical Research, which is an institution independent from the study group, managed the randomization process. The flow of participant recruitment is shown in Figure 1.

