### Statistical Analysis

Statistical analyses and reporting of this trial will be based on the intention-to-treat approach. Analyses with complete samples will be also performed to verify the robustness of the results.

The full analysis data set will include all randomized subjects who underwent at least 1 procedure of the intervention.

For baseline variables, we will generate summary statistics with proportions and frequencies for categorical variables and means and SDs for continuous data. For primary and secondary outcome analyses, we will analyze the mean changes from baseline using the MMRM method. Analyses conducted using the MMRM method will include the fixed and categorical effects of intervention, time, and the intervention × time interaction. Imputation will not be performed for missing values, because mixed models can deal with missing data through the maximum likelihood. All comparisons are planned, and all *P* values will be 2-sided. The significance level will be set at 5% for all statistical analyses. All analyses will be conducted using Stata version 16 (StataCorp).

We will also conduct a multivariate analysis to verify the predictors and mediators of the primary and secondary outcomes. A detailed analytical plan will be presented separately.

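### The 166 participants required correspond to 80% power at effect size 0.44 in a plain two-group comparison, not to the 90% (β .10) printed beside them

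*Protocol article*

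**What the plan says.** All the inputs are printed in the protocol article.

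- **Error rates.** The Sample Size section says the primary outcome will be analysed by MMRM to "compare the amount of change between groups before and after the intervention (α .05, β .10").
- **Effect size.** The same section takes its effect from "a study that showed the effect of MBPs on the quality of life (effect size=0.44"), because the authors knew of no published effect on presenteeism.
- **Result.** "We estimated that a total of 166 participants are required; however, the sample size was set at a maximum of 220 participants", the increase being an allowance for an assumed 25% dropout.
- **Sidedness and level.** The Statistical Analysis section adds "All comparisons are planned, and all *P* values will be 2-sided" and "The significance level will be set at 5% for all statistical analyses".
- **Allocation.** The Randomization section says that participants were "randomly allocated to either the bMBCT or the waitlist control group (in a 1:1 ratio").

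The Sample Size section gives no within-person correlation, no number of repeated measures and no variance reduction as an input to the calculation.

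**The concern.** The section prints α, β, effect size and N together, so a reader can check whether they agree. As a two-group comparison they do not: the N is about three quarters of what β .10 requires (166/220 = 0.75). This is not a detail that a condensed article may leave to a fuller document, because the figures that disagree are all in the article.

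The stake is how a null or inconclusive result on productivity would be read. The effect size is borrowed from quality of life, so such a result is a real possibility. A reader would then weigh it against a stated 10% chance of missing an effect of 0.44, when on the printed inputs a two-group comparison has a chance of about 20%.

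**Working it through.** **Inputs.** Standardised difference d = 0.44, α = 0.05, β = 0.10, N = 166, dropout 25% and a maximum of 220 (Sample Size); two-sided tests at 5% (Statistical Analysis); 1:1 allocation (Randomization).

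**Step 1: normal approximation.** n per arm = 2(z₁₋α/₂ + z₁₋β)²/d².

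- 90% power: 2 × (1.960 + 1.282)²/0.44² = 108.5, so 109 per arm and 218 in total.
- 80% power: 2 × (1.960 + 0.842)²/0.44² = 81.1, so 82 per arm and 164 in total.

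**Step 2: two-sample t-test (noncentral t).**

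| Power | n per arm, solved | Rounded up | Total |
|---|---|---|---|
| 80% | 82.05 | 83 | **166** |
| 90% | 109.5 | 110 | 220 |

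The plan's 166 is reproduced exactly at β .20 and is not reproduced at β .10. With 82 per arm, power is 79.97%, just short of 80%, which explains why the answer is 83 per arm.

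**Step 3: power at the planned numbers (t-test).**

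- 166 analysed: 80.5% (80.9% by normal approximation).
- Completers left from the maximum: 220 × 0.75 = 165, power 80.2%.
- 220 analysed: 90.1%. This requires no dropout, whereas the section raises the number to 220 to absorb dropout.
- The dropout allowance itself is sound: 166/0.75 = 221.3, close to 220.
- For scale only, 90% power at d = 0.44 after 25% dropout would need 220/0.75 = 293.3, so 294 enrolled (218/0.75 = 290.7, so 291, by normal approximation).

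**Step 4: effect detectable at 90% power with 83 per arm.** Normal approximation: (1.960 + 1.282) × √(2/83) = 0.503. t-test: 0.506, about 0.51, against 0.44 in the plan.

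**Step 5: could another simple calculation have given 166?**

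- One-sided 5%, t-test: 130 in total at 80% power and 180 at 90%; at 166 the power is 88.1%. It also conflicts with the two-sided rule.
- Bonferroni over the three time points (normal approximation): 218 at 80% and 280 at 90%.

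Neither gives 166.

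**Step 6: could repeated measures give 90% at 166?** For 90% power at 83 per arm, the variance must fall to (0.44/0.506)² = 0.756 of its raw value. Suppose that 0.44 is scaled to the raw-score SD and that any two visits have the same correlation ρ. Both are assumptions; the article states neither.

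| Analysis | Variance factor | ρ for 90% at 166 |
|---|---|---|
| One visit, adjusted for baseline | 1 − ρ² | about 0.49 or higher |
| One visit, change score | 2(1 − ρ) | about 0.62 or higher |
| Mean of three change scores | (1 + 2ρ)/3 − 2ρ + 1 | about 0.43 or higher |
| Mean of three follow-up scores, no baseline | (1 + 2ρ)/3 | about 0.63 or lower |

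The gain is not guaranteed. For a single-visit change score at 83 per arm, power is 73.0% at ρ = 0.4, 80.5% at ρ = 0.5 and 88.3% at ρ = 0.6. If 0.44 is already the standardised difference in change at a single visit, the baseline correlation brings no further gain through the change score.

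**The case against.** The strongest reply is that the planned analysis is an MMRM of change from baseline with three follow-up assessments, not a single t-test. Step 6 shows that 166 can reach 90% power by several routes, and that most of them need no baseline covariate. A t-test figure is therefore not the power of the planned analysis, which may lie above or below 80%. The 165 is also a completer count: under maximum likelihood, people who leave after the week 4 assessment still contribute data.

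This stands as far as it goes, and it rules out two stronger readings:

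- **That the trial really runs at 80% power.** The documents do not support this, because the correlation on which MMRM power depends is not given. The 80% holds for a plain two-sample comparison.
- **That the absence of a baseline term from the listed model effects proves that 90% is out of reach.** It does not. Baseline already enters through the change score, and a covariate may be specified in a fuller document that is not shown.

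The reply does not rescue the section as printed. No correlation, number of measures or variance reduction is stated, so the printed inputs do not lead to the printed N. A correlation-based calculation could have landed on the exact t-test answer for 80% power, but only by coincidence.

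It may also be said that only wording is affected and that a null result would be read from its confidence interval. That is fair, and it limits the consequence. The power statement is still wrong as printed for the primary outcome.

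**Conclusion.** The point holds in a conditional form. With effect size 0.44, two-sided α .05 and 1:1 allocation, a two-sample comparison needs 220 analysed for β .10; the stated 166 is the answer for β .20. On that basis the type II error is about twice the one printed (19.5% against 10%).

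This rests on reading 0.44 as a standardised between-group difference tested in a single comparison, which is the only calculation the printed inputs allow. It would be overturned only if 166 came from a repeated-measures calculation whose inputs are not reported. That is possible but unlikely given the exact match. The enrolment maximum, the dropout allowance and the type I error rate are not in question here.

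**What to change.** Restate the Sample Size section as β .20 (80% power) for 166 analysed and a maximum of 220 enrolled.

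Keep β .10 only if 166 came from a repeated-measures calculation made at the design stage. In that case state the correlation and the number of measures that the calculation actually used. A correlation solved backwards to fit 166 should not be reported, and the primary model should not be altered to justify the number.

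No extra enrolment is proposed, and data collection and the analysis stay as they are. The cost is a change of wording in one section and, if β is corrected, a less favourable stated power.

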### Statistical Analysis

Statistical analyses and reporting of this trial will be based on the intention-to-treat approach. Analyses with complete samples will be also performed to verify the robustness of the results.

The full analysis data set will include all randomized subjects who underwent at least 1 procedure of the intervention.

For baseline variables, we will generate summary statistics with proportions and frequencies for categorical variables and means and SDs for continuous data. For primary and secondary outcome analyses, we will analyze the mean changes from baseline using the MMRM method. Analyses conducted using the MMRM method will include the fixed and categorical effects of intervention, time, and the intervention × time interaction. Imputation will not be performed for missing values, because mixed models can deal with missing data through the maximum likelihood. All comparisons are planned, and all *P* values will be 2-sided. The significance level will be set at 5% for all statistical analyses. All analyses will be conducted using Stata version 16 (StataCorp).

We will also conduct a multivariate analysis to verify the predictors and mediators of the primary and secondary outcomes. A detailed analytical plan will be presented separately.

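### A complete-sample analysis cannot verify the robustness of the MMRM to missing data, because it rests on a stronger assumption than the MMRM does

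*Protocol article*

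**What the plan says.** Protocol article, Statistical Analysis:

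- On the main analysis: "we will analyze the mean changes from baseline using the MMRM method". The listed model terms "will include the fixed and categorical effects of intervention, time, and the intervention × time interaction". No baseline or other covariate is listed.
- On missing values: "Imputation will not be performed for missing values, because mixed models can deal with missing data through the maximum likelihood".
- On the check, placed directly after the intention-to-treat statement: "Analyses with complete samples will be also performed to verify the robustness of the results". What counts as a complete sample is not defined.

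The article names no other missing-data sensitivity analysis. The analytical plan that it promises separately concerns predictors and mediators.

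The Sample Size section assumes 25% dropout, citing 23% in an earlier online workplace programme. The Blinding section states that participants and therapists know the allocation and that every measurement is self-reported.

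**The concern.** A robustness check is useful when it relaxes an assumption of the main analysis. This one tightens it. Maximum likelihood in the MMRM is valid if dropout depends only on data already observed (missing at random, MAR). A comparison of mean change among complete cases, with no covariates, needs dropout to be essentially unrelated to outcome within each arm (missing completely at random, MCAR).

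Two consequences follow. If dropout depends on an observed earlier score, the check can disagree although the MMRM is right. If dropout depends on the score that was never recorded (missing not at random, MNAR), both analyses are biased and may agree. Early loss is the extreme case: the model is fitted to change scores, so a participant with no post-baseline value contributes to neither analysis.

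The question has weight here because about a quarter of participants are expected to be lost, the outcome is a self-rating, participants know their arm, and the comparator is a waitlist. A reader told that robustness has been verified would take reassurance that the check cannot give.

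**Working it through.** **1. The plan's own dropout figure.** Inputs from Sample Size: 166 required, 25% dropout, maximum 220.

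166 / (1 − 0.25) = 221.3, so 222 against 220 stated; in reverse, 220 × 0.75 = 165. The step reproduces to within 2 participants. At 25% loss, 0.25 × 220 = 55 participants lack complete data.

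**2. Do the two analyses agree when they should?** Simulation, 3,000 trials per scenario, 220 participants allocated 1:1. These settings are assumptions, not in the documents: correlation 0.6 between visits, about 25% loss per arm by the last visit, random loss in the waitlist arm, and loss in the bMBCT arm more likely with poor change (except under MCAR). MMRM here means maximum likelihood on the three change scores. Mean estimates at the last visit, in SD:

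| Dropout in bMBCT arm | True effect | MMRM | Complete cases |
|---|---|---|---|
| MCAR | 0.44 | 0.44 | 0.44 |
| MAR (depends on previous observed change) | 0.44 | 0.44 | 0.57 |
| MNAR (depends on current, unseen change) | 0.44 | 0.57 | 0.61 |
| MNAR, all loss before first post-baseline visit | 0.44 | 0.56 | 0.56 |
| MAR | 0 | 0.00 | 0.13 |
| MNAR | 0 | 0.13 | 0.17 |
| MNAR, all loss before first post-baseline visit | 0 | 0.12 | 0.12 |

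The gap is widest under MAR, where the MMRM is right (0.57 − 0.44 = 0.13). It is 0.04 under MNAR across visits, where the MMRM is too high by 0.57 − 0.44 = 0.13. It is zero in every simulated trial when all loss is early, where both are too high by 0.12.

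A separate large-sample simulation, with bMBCT dropout depending on the observed week-4 change and correlation 0.4 to 0.6, gave 0.44 for the likelihood estimate and 0.49 to 0.62 for complete cases. That mechanism is MAR, so it shows a false alarm and not false confirmation.

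**3. What a check that relaxes MAR would report.** Assumptions: 83 analysed per arm (166 / 2), 25% dropout in the bMBCT arm only, standard error held fixed, two-sided 5% test with critical value 1.974.

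- SE = √(2/83) = 0.155 SD.
- If missing bMBCT values are worse than MAR predicts by δ, the estimate becomes observed effect − 0.25 × δ.
- Significance is lost when δ = (observed effect − 1.974 × 0.155) / 0.25.
- Observed effect 0.35: (0.35 − 0.306) / 0.25 ≈ 0.17 SD.
- Observed effect 0.44: (0.44 − 0.306) / 0.25 ≈ 0.53 SD, more than the whole planned effect.

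**4. One fixed scenario.** If bMBCT dropouts keep no benefit, 0.44 × 0.75 = 0.33 SD. Then z goes from 0.44 / 0.155 = 2.83 to 0.33 / 0.155 = 2.13, still above 1.974.

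**The case against.** **Scope.** A journal protocol leaves much to the SAP, which is not shown and may contain further sensitivity analyses. This stands, and the point is not that such analyses are absent. The article itself fixes a check, states what the check achieves, and excludes imputation in terms that would also exclude the usual imputation-based sensitivity analyses.

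**Meaning of the check.** The sentence follows the intention-to-treat statement and comes before the missing-data sentence, so it may intend a contrast between all randomised participants and programme completers. This ambiguity stands. It does not rescue the claim, because an analysis of programme completers does not test departures from MAR either.

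**Leaving the programme is not the same as missing a questionnaire.** Assessments are collected electronically, nothing ties them to session attendance, and the 25% is not broken down by type of loss. This stands. It is why assigning a waitlist trajectory to bMBCT dropouts is one scenario among several and not the obvious check.

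**Stronger readings.** A reader might infer that the MMRM will overstate the benefit. The documents do not support that: they give no evidence that dropout is MNAR or concentrated in the bMBCT arm. Waitlist participants, who wait 7 months, could also leave for outcome-related reasons, which could change the size or direction of any bias. A reader might also infer that the planned conclusion is fragile. At the planned 0.44 SD it survives the loss of all benefit among bMBCT dropouts; the 0.17 SD tipping shift belongs to an observed effect chosen for illustration. No loss of power is claimed, because 166 with effect size 0.44 does not correspond to the stated β of .10 in a plain two-sample calculation, which is a separate matter.

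**Conclusion.** The point holds as one about what the named check can show. On the complete-case reading it needs roughly MCAR within arm, against MAR for the MMRM, so agreement does not verify robustness to missing data and disagreement does not show that the MMRM is wrong. On the programme-completer reading it does not address the question.

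The MMRM itself is not faulted. The biases of 0.12 to 0.17 SD in the MNAR scenarios depend on assumed mechanisms and only illustrate that both analyses can be wrong together. The tipping shifts of 0.17 and 0.53 SD rest on 83 analysed per arm, dropout effects confined to the bMBCT arm and a fixed standard error. They show how far the answer depends on the effect observed, which is what the planned check would leave unreported. This is a worthwhile, cheap improvement and not a fatal flaw.

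**What to change.** In Statistical Analysis:

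1. Keep the MMRM as the main analysis and state that the no-imputation rule applies to that analysis only.
2. Define complete samples, report that result descriptively, and remove the claim that it verifies robustness.
3. Name a delta-adjusted tipping-point analysis of absolute presenteeism as the robustness check for missing data. Shift the missing values in the bMBCT arm, and also in the waitlist arm, over a range fixed in advance in scale points. Report the combinations at which the conclusion changes, and say beforehand which shifts would be regarded as plausible.
4. Reference-based imputation, with bMBCT dropouts following the waitlist trajectory, may be added as one further scenario.

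The cost is a few sentences and some programming, with no new data and no change to design or sample size. The downside is that the sensitivity result may look less favourable than the complete-sample one.

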## Methods

### Participants

We started recruiting participants in August 2021. The intervention is ongoing and is scheduled to be completed in December 2023. The study is being conducted at the Keio University Center for Stress Research in Tokyo, Japan. The participants are being recruited from among the employees of 3 companies in different industries: Daiwa Securities Group Inc (security), Kumon Institute of Education Co, Ltd (education), and Nichirei Corporation (processed foods). Participants are eligible for the study if they meet the following criteria: (1) aged between 20 and 65 years, (2) work longer than 30 hours weekly, (3) have no history of sick leaves longer than 1 month due to mental disorders or have recovered for longer than 6 months after a sick leave, (4) have physical illnesses but are judged fit to participate in the research by the investigators, (5) score 8 or less in the absolute presenteeism item of the World Health Organization Health and Work Performance Questionnaire (WHO-HPQ), (6) can participate in the intervention and respond to the questionnaires via the internet, and (7) can provide written informed consent. Eligible participants are excluded if they (1) have previously participated in a mindfulness-based intervention for 8 weeks or longer, (2) are unlikely to participate during the research period (eg, they plan to move/relocate), and (3) are judged by the investigators as unfit to participate in the intervention due to physical conditions and other reasons (eg, unstable internet connection). Candidates who score higher than 8 on the WHO-HPQ absolute presenteeism item are allowed to participate in the intervention but will not be included in the RCT. The obtained data will be included in the multivariable analysis described later.

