### Control Group

Participants in the control group will wait until the intervention group has completed the intervention. During this waiting period, they have been requested not to attend other mindfulness or meditation activities. After the waiting period is completed (ie, 7 months after allocation), the participants in the control group will be offered the same bMBCT but without monthly follow-up sessions.

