### Outcomes

#### Primary Outcome

The primary outcome of this study is the mean difference in absolute presenteeism (measured using the WHO-HPQ) between the intervention and the waitlist control (ie, before bMBCT offered) groups at 4 weeks, 3 months, and 6 months postintervention.

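### The full analysis set requires receipt of an intervention procedure, which conflicts with the stated intention-to-treat analysis and cannot be applied to the waitlist arm

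*Protocol article*

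**What the plan says.** The Statistical Analysis section opens with the principle: "Statistical analyses and reporting of this trial will be based on the intention-to-treat approach". It then defines the analysis population: "The full analysis data set will include all randomized subjects who underwent at least 1 procedure of the intervention". No other primary set is defined. The article does not explain what counts as a procedure of the intervention and gives no counterpart for the control arm.

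The Control Group section describes what controls do in the meantime: "Participants in the control group will wait until the intervention group has completed the intervention". They are offered the programme later: "After the waiting period is completed (ie, 7 months after allocation), the participants in the control group will be offered the same bMBCT". The Primary Outcome section fixes the contrast as one "between the intervention and the waitlist control (ie, before bMBCT offered) groups at 4 weeks, 3 months, and 6 months postintervention".

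On missing outcomes, the Statistical Analysis section says: "Imputation will not be performed for missing values, because mixed models can deal with missing data through the maximum likelihood". The outcome modelled is the mean change from baseline.

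**The concern.** An intention-to-treat comparison keeps everyone who was randomised, in the arm to which they were randomised. The analysis set adds a condition met or failed after randomisation, namely having received some of the treatment. One arm is given that treatment during the comparison and the other is not, so the condition can act only on one side.

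According to the Blinding section, participants know their allocation, and every measure is self-reported. Sessions are held outside working hours (Interventions), so whether a person starts could plausibly be tied to workload or motivation, and either could be related to self-rated work performance. Once people are removed from one arm on such grounds, randomisation no longer guarantees that the arms are comparable. Two sentences that cannot both be followed also leave the primary population to be settled when the analysis is done, possibly after outcomes have been seen.

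**Working it through.** The defect is one of definition, and no figure stated in the article changes. The passages have to be set side by side.

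**Can a control participant meet the criterion?**

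- Control Group: controls wait, and are offered bMBCT 7 months after allocation.
- Primary Outcome: control data are those taken before bMBCT is offered.
- Table 2, the schedule for all participants: the Waitlist row is marked not applicable in every column.
- Table 3: the Waitlist row carries intervention marks in weeks 1 to 4. These belong to the later course given once waiting is over, as the Control Group section describes.

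No control participant can therefore undergo an intervention procedure in the period being compared.

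**What does the rule then do?**

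1. Applied literally to the compared period, no control qualifies.
2. Applied literally to the whole study, only controls who later start bMBCT qualify. That selects them on an event after the 6-month endpoint.
3. Applied to the bMBCT arm alone, never-starters leave that arm and all controls stay.

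None of the three is an intention-to-treat set. Only the third yields a usable comparison, so it is the one likely to be applied.

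**Size, as an illustration only.** The article gives no never-start rate and nothing about never-starters' outcomes, so the values of f, g and r below are assumptions.

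Let f be the share of the bMBCT arm that never starts, and g the amount in SD by which never-starters' mean change falls short of starters'. If all never-starters give follow-up data, dropping them moves the arm mean, and so the contrast, by f × g. The yardstick is the planned effect size of 0.44 (Sample Size).

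- f = 5%, g = 0.2: 0.05 × 0.2 = 0.010 SD; 0.010 / 0.44 = 2%.
- f = 10%, g = 0.5: 0.10 × 0.5 = 0.050 SD; 0.050 / 0.44 = 11%. At 220 participants allocated 1:1, this is 11 of 110 people.
- f = 25%, g = 0.5: 0.25 × 0.5 = 0.125 SD; 0.125 / 0.44 = 28%.

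If only a share r of never-starters respond (and, for simplicity, all starters do), their weight among responders is f × r / (1 − f + f × r). With f = 10% and r = 50% this is 0.05 / 0.95 = 0.053, and the shift is 0.053 × 0.5 = 0.026 SD. With r = 0 there is no shift. If never-starters change for the better relative to starters, g is negative and the shift reverses.

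**The case against.** The strongest defence is that nobody would apply the rule so as to lose the control arm. A reader might infer from the literal wording that the trial would be left with no controls. The aim, the primary outcome and the sample size section all presuppose a comparison between groups, so that is not what the authors intend. This is accepted. The literal reading shows only that the criterion does not fit a waitlist arm. It does not predict what will be run.

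A second defence is that the effect may be small or nil. The model uses changes from baseline without imputation, so a never-starter with no follow-up questionnaire contributes no change score under either definition. The set matters only for never-starters who still respond. A stable difference in level also cancels in a change score, so only a difference in change counts. Even the 0.05 SD illustration is about a third of a standard error, taking a simple two-group comparison at 83 per arm (half of the required 166): √(2/83) = 0.155 SD, and 0.05 / 0.155 = 0.32. All of this stands, and it limits what can be said about size. It does not make the definition consistent.

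Third, procedure might have been meant to cover study assessments, or the MMRM might not use this set. The sentence ties the procedure to the intervention, and no other primary set is given. If something else was meant, the sentence still needs correcting. Nor can this be left to a separate analysis plan, because the article states a rule and the rule is faulty.

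**Conclusion.** The point holds as an inconsistency in the primary analysis population. The article commits to intention-to-treat and defines a set that is not intention-to-treat and cannot be applied to both arms. In practice it would drop never-starters from the bMBCT arm only, in an unblinded trial, and so break the randomised comparison.

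The bias has no size or direction that the document supports. The figure of 0.05 SD against 0.44 rests on three assumptions: 10% never starting, complete follow-up among them, and a change 0.5 SD worse. A reader might infer that the rule favours bMBCT because non-starters are busier or less motivated. The article says nothing about non-starters, and busy employees need not report a worse change in their own performance.

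Two neighbouring statements might be read as part of the same fault, and are not. The complete-sample analysis ("Analyses with complete samples will be also performed to verify the robustness of the results") is a weak check, because it generally needs a stricter missing-data assumption than the MMRM. It is only an addition, however, and its replacement is a choice for the analysis plan. Candidates scoring above 8 are kept out of the randomised comparison. Their data ("The obtained data will be included in the multivariable analysis described later") enter an exploratory analysis whose methods the article expressly defers.

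**What to change.** Replace the sentence defining the full analysis set. The set should be all randomised participants, analysed in the arm to which they were allocated, regardless of attendance, with all available outcome data entering the MMRM. If the investigators want results for people who began the programme, keep attendance at one or more sessions as the criterion for a clearly labelled supplementary (per-protocol) set, not for the primary comparison. Make the change before outcome data are examined by arm.

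The cost is one corrected sentence. The MMRM itself is unchanged, and no new data collection is needed, because the assessment schedule already covers all participants whether or not they attend. The estimate may be slightly diluted by including people who received no sessions, which is what an intention-to-treat comparison is meant to reflect.

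### The stated MMRM for change from baseline omits the baseline score and company, the two randomisation strata, and so gives a conservative, less efficient test

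*Protocol article*

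**What the plan says.** Under Randomization, allocation is 1:1 and "The participants were assigned a computer-generated random number stratified according to company and the baseline WHO-HPQ absolute presenteeism score". There are three companies; the cut-points for the presenteeism strata are not given.

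Under Statistical Analysis, for primary and secondary outcomes alike, "we will analyze the mean changes from baseline using the MMRM method". The model is then described: "Analyses conducted using the MMRM method will include the fixed and categorical effects of intervention, time, and the intervention" by time interaction. No baseline score, company or other stratification term is named for this model anywhere in the article. The analysis plan that is to be presented separately is the one for predictors and mediators (Multivariable Analysis; end of Statistical Analysis), not the primary comparison.

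Under Sample Size, the MMRM is described only as a way "to compare the amount of change between groups before and after the intervention (α .05, β .10").

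**The concern.** Stratifying on a factor balances it between arms. If the analysis then leaves that factor out, the variation it explains stays in the residual, and the reported standard error describes a noisier experiment than the one that was run.

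Taking change from baseline does not supply the missing term. It forces the slope on baseline to be 1, whereas a single 0-10 self-rating is likely to have a slope well below 1. Fitting baseline as a further time level, with an unconstrained arm-by-time term, gives the same contrast when data are complete, so that reading does not help either.

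At stake is power on the primary outcome, and on every secondary outcome because the same model serves them all.

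**Working it through.** **Inputs from the article.** Two-sided tests ("all *P* values will be 2-sided"), α 0.05, β 0.10, effect size 0.44 borrowed from quality of life, 166 required, maximum 220 with 25% dropout (220 × 0.75 = 165), 1:1 allocation, strata as above.

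**Assumed.** ρ = 0.3, 0.5, 0.7; the SD to which 0.44 refers (both readings shown); one post-baseline visit; where company matters, it adds 5% of the outcome variance.

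**1. The plan's own figure.** Per arm n = 2(z₁₋α/₂ + z₁₋β)²/d².
- β = 0.10: 2 × (1.960 + 1.282)²/0.44² = 108.5, so 109 per arm and 218 in total (220 by t-test).
- β = 0.20: 81.1, so 82 per arm and 164 in total (166 by t-test).

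A plain two-group formula therefore gives 166 at 80% power, not 90%. However, 166 at 90% can also be reached with an unstated ρ: about 0.62 for a change-score analysis, or about 0.49 for a baseline-adjusted one.

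**2. Model-based variance.** With equal variances at baseline and follow-up, Var(change) ∝ 2(1−ρ) and Var(adjusted) ∝ 1−ρ². The ratio adjusted/change is (1+ρ)/2.

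| ρ | ratio | inverse, 2/(1+ρ) | SE smaller by |
|---|---|---|---|
| 0.3 | 0.65 | 1.54 | 19% |
| 0.5 | 0.75 | 1.33 | 13% |
| 0.7 | 0.85 | 1.18 | 8% |

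**3. Power by formula, 83 per arm.** If 0.44 is in change-SD units, the non-centrality is 0.44 × √(166/4) = 2.834 and power is Φ(2.834/√ratio − 1.96).

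| ρ | change-SD units: stated → adjusted | outcome-SD units: stated → adjusted |
|---|---|---|
| 0.3 | 80.9% → 94.0% | 66.8% → 84.4% |
| 0.5 | 80.9% → 90.5% | 80.9% → 90.5% |
| 0.7 | 80.9% → 86.7% | 95.5% → 97.8% |

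With company variance of 0.05 added and company in the adjusted model, the ratio is (1−ρ²)/(2(1−ρ)+0.05):
- ρ = 0.3: 0.91/1.45 = 0.628
- ρ = 0.5: 0.75/1.05 = 0.714
- ρ = 0.7: 0.51/0.65 = 0.785

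In change-SD units the adjusted power is then about 95%, 92% and 89%.

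**4. Simulation of the stratified design.** 166 participants, permuted blocks of 4 within 3 companies × baseline strata.
- *Type I error, nominal 5%* (median split; first figure without and second with a company effect). Stated model: 2.6% and 2.2% at ρ = 0.3; 3.1% and 3.1% at 0.5; 4.0% and 2.9% at 0.7. With baseline and company in the model: 4.5% to 5.3%.
- *Power, change-SD units, company at 5% of variance.* Stated model: about 82-85%. With both covariates: about 89-95%. The stated model does slightly better than the 80.9% in step 3 because the stratified estimate varies less than its standard error claims.
- *True sampling variance of the primary estimate.* Adjustment lowers it by about 15%, 12% and 7% (ρ = 0.3, 0.5, 0.7) with a median split, and by about 10%, 7% and 3% with quartile strata. Across the stratum definitions tried, the fall is about 4-20%, with 3% in the least favourable cell.

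For the primary outcome, then, most of the shortfall lies in an overstated standard error and less of it in the estimator itself.

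**The case against.** **The list may not be exhaustive.** Saying that the model will include three effects does not exclude others, and an article may leave covariates to an unseen plan. This stands in part. But the article chose to state the model, and a reader would take the three terms as the model. Covariance structure is different: the article says nothing on it, and that is fairly left to the analysis plan.

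**The design already protects the primary outcome.** This stands. A reader might take the 35%, 25% and 15% reductions implied by (1+ρ)/2 as true gains in precision. For presenteeism they are not, because its own baseline is a stratifier. For the same reason, chance baseline imbalance is mainly a concern for secondary outcomes, whose baselines are not stratified.

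**The stated analysis is valid.** This stands too. A reader might infer that P values not matched to the randomisation endanger the trial's conclusions. The simulated error rates lie below 5%, so the test is conservative and the contrast unbiased.

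**The trial has not been shown to be powered at 80%.** A reader might infer this from step 1, but it depends on an unstated correlation and SD. It is a separate matter to reconcile and carries no weight here.

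**The eligibility cap could shrink the gain.** Only scores of 8 or less enter the RCT, which narrows the baseline range. If baseline variance falls to 70% of its unselected value with the slope unchanged, the ratio is (1−ρ²)/(0.7(1−ρ)² + 1−ρ²) = 0.73, 0.81 and 0.89. Power in change-SD units still rises from 81% to about 91%, 88% and 85%.

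**Company may add little.** This stands: in simulation with 0.44 in outcome-SD units it added at most about 1.5 points of power beyond baseline.

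**Conclusion.** The point holds as a conservative loss of efficiency. The stated model leaves out both factors on which randomisation is stratified, so its standard error is too large: the variance is 1.54, 1.33 and 1.18 times the baseline-adjusted one at ρ = 0.3, 0.5 and 0.7. For the primary outcome the test runs at about 2-4% instead of 5%. In change-SD units with company at 5% of variance, about 82-85% power is obtained where 89-95% was available; without a company effect, the adjusted range by formula is 87-94%. In outcome-SD units at ρ = 0.7 the gain is only about 2 points. Most of the benefit comes from the baseline term.

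These sizes rest on an assumed ρ, assumed stratum cut-points, a single follow-up visit and about 166 analysed. The MMRM uses three visits and partial data by maximum likelihood, so the exact figures will differ. The direction will not: adjustment costs almost nothing and can only be expected to help.

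**What to change.** State in the Statistical Analysis section that every MMRM includes, besides intervention, time and their interaction, the baseline value of the outcome analysed, baseline by time, and company as a fixed effect. In the secondary-outcome models also keep baseline WHO-HPQ absolute presenteeism, since it is a stratifier. Give the presenteeism cut-points used at randomisation. Record the change before outcomes are examined by arm, so that the covariates are not chosen post hoc.

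Company is known at randomisation and all baseline scores are collected under Baseline Assessment, so no new data are needed. The treatment contrast at each visit keeps its meaning. The cost is a few degrees of freedom.
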